## Methods

### Trial design

This trial will employ a two-arm hybrid type III cluster-randomized controlled superiority trial design (28). Each cluster, or “Primary Health Center (PHC)”, is the unit of randomization, with equal allocation of clusters between arms.

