The teams at all 14 PHCs were trained on the World Health Organization's (WHO) mhGAP intervention guide (5), previously adapted for Sehore district (14). The MOs were trained through in-person and virtual modes, depending on their availability to attend in-person training, over eight days in the diagnosis, treatment and referral of positive cases of depression, including the option for referring patients to receive HAP delivered by ASHAs (29). The training for ANMs and nurses was conducted separately, as part of a 2-day in person training with instruction on screening of outpatients for depression, and referral and tracking of depression cases. Training for ANMs and nurses emphasized case detection and screening outpatients using the PHQ-2, and entering data into a “Screening Record Register” to track screening rates, refusal, patient willingness to be contacted by the research team (to participate if they screen positive), and referral to the MO and initiation of treatment. The PHQ-2 is a screening questionnaire for depression which comprises two items of the widely used and contextually validated PHQ-9. The PHQ-2 was selected to increase the quality and efficiency of screening conducted by ANMs/Nurses, and its use, instead of the full 9 item version, is supported by prior studies showing that the positive predictive value for the presence of “any depressive disorder” is 75% for a score of ≥3 (38). Further, the health system in India has planned to adopt the PHQ-2 for community-level depression screening (39). Each trial arm will have 7 PHCs, with estimated total staffing of 14 MOs (2 per facility), 14 nurses (2 per facility), and 7 ANMs (1 per facility), with some variation in staffing expected between facilities.

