### Sample size estimation

Based on prior outpatient footfall data from participating PHCs, it is estimated that roughly 178 adult outpatients will attend each PHC per month; thus, over a 12-month period of delivery of the Enhanced Implementation Support strategy, there will be approximately 14,994 patients attending facilities in each arm. Assuming about 10% of these patients [based on prior case detection data in the region (14)] will refuse screening or will be excluded at the discretion of the ANM/nurse, the resulting estimates work out to about 13,494 outpatients available for screening in each arm. This sample size will allow us to detect a 15% difference in the proportion of PHQ-2 screenings between arms, assuming that 10% of patients are screened in the Routine Implementation Support Arm, at 80% power, an inter-cluster coefficient of variation of 0.5 (calculated from background facility data on adult outpatient footfall and existing NCD screening rates) and an intra-cluster correlation (ICC) of 0.05 (52).

Proportions (and not numbers of screenings) will be used to account for the between-facility variation in outpatient footfall.

The earlier PRIME study conducted in the same region achieved a 12% depression screening rate in its facility detection survey component (14), and assuming an additional contribution by the various components of enhanced implementation support (i.e., fortnightly coaching calls, WhatsApp support and monthly peer-learning conferences) to further increase the depression screening rate, we will hypothesize a 25% screening rate in the intervention arm, or a 15% between-arm difference in screening rates. We have referred the formula for calculating sample size for parallel cluster randomized controlled trials with fixed number of clusters (*n* = 14 in this study) by Hemming et al. 2020 (52).

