### Statistical analysis

All analyses of implementation outcomes will be intention-to-treat comparisons between arms. Generalized linear regression models with a log link will be used to compare facility-level implementation outcomes, including the primary outcome of proportion of patients screened on the PHQ-2. ANCOVA analyses will be conducted for comparing secondary implementation outcomes between arms. Time by study arm interactions will be explored using a growth curve model to inspect non-linear trends in the progress of the screening, number of patients who screen positive, referral to MO and treatment initiation. Descriptive statistics will be used for comparing exploratory measures of facility readiness and context assessment between arms. The process indicators from the PDSA coaching sessions will be used for descriptive analysis, to quantitatively assess fidelity to the protocol for Enhanced Implementation Support. Logistic regression models will be used to compare the proportion of patients who remit on the PHQ-9, defined as score <5, between arms at 3-month follow-up. Possible covariates will be entered into the models, including age or gender of the patients, as well as adjusting for cluster effects. Linear regression models will be used to assess differences in the change in disability (WHODAS 2.0) and anxiety (GAD-7) outcomes at 3-month follow up, with baseline values as covariates to adjust for any baseline inter-cluster differences. Stata version 17.0 will be used for all statistical analyses and *p*-values <0.5 will be considered statistically significant.

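### The WHODAS 2.0 and GAD-7 linear models are specified with a baseline covariate but no clear provision for correlation within PHCs; if that covariate is the only provision, p-values and intervals will be too optimistic.

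*Protocol article*

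**What the plan says.** The PHC "is the unit of randomization, with equal allocation of clusters between arms" (Trial design), and "Each trial arm will have 7 PHCs" (Facility eligibility and recruitment). Table 4 lists three patient-level outcomes: PHQ-9 remission, WHODAS 2.0 and GAD-7.

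The Statistical analysis section takes these outcomes in three consecutive sentences:

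1. Logistic regression is planned for PHQ-9 remission.
2. The next sentence reads "Possible covariates will be entered into the models, including age or gender of the patients, as well as adjusting for cluster effects".
3. The third sentence gives the other two outcomes linear regression models for the change at 3 months. Its only further specification is "with baseline values as covariates to adjust for any baseline inter-cluster differences".

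The third sentence names no random effect, cluster-robust variance or cluster-level analysis. The baseline score is the only device in it that is tied to clusters.

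The Sample size estimation section does allow for clustering, with "an intra-cluster correlation (ICC) of 0.05" and "an inter-cluster coefficient of variation of 0.5", but for the screening outcome only. No enrolment target, ICC or power is given for WHODAS 2.0 or GAD-7.

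**The concern.** Two different problems arise when facilities are randomised and patients are measured. One is that PHCs may differ at baseline, and a patient-level baseline covariate helps with that. The other is that follow-up outcomes of patients in the same PHC are correlated even after baseline adjustment. This second problem determines the standard error of the arm effect, and a baseline covariate does not solve it. A linear model without a cluster term treats every patient as an independent unit, although the comparison rests on 7 PHCs against 7.

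The order of the sentences gives the linear models their own provision for inter-cluster differences, separate from the cluster adjustment mentioned just before. An analyst who followed that sentence literally would report standard errors that are too small for two of the three patient outcomes. Table 4 states a directional hypothesis of a significant difference for both.

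**Working it through.** **The plan's own figure (primary outcome).** It is stated as "assuming that 10% of patients are screened in the Routine Implementation Support Arm, at 80% power", with 25% in the intervention arm.
- Attendance: 178 × 12 × 7 = 14,952 per arm, against 14,994 stated (178.5 per month gives it exactly). 14,994 × 0.9 = 13,494.6, which matches the stated 13,494.
- Per PHC: m = 13,494 / 7 = 1,927.7.
- Design effect, reading 0.5 as the coefficient of variation of cluster size: 1 + ((1 + 0.5²) × 1,927.7 − 1) × 0.05 = 121.4. Effective n = 13,494 / 121.4 = 111.1 per arm.
- Power at an assumed two-sided 5% level: 78.7% with a t reference on 12 df, and 84.2% to 85.1% with normal approximations.

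The stated 80% is reproduced to within 2 points by the t-based version. The design therefore does recognise clustering.

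**The two linear models, if clustering is not modelled.** Inputs that the document does not give are assumed:
- Patients per PHC: m = 10 to 30.
- ICC: 0.05 (borrowed from screening) or 0.01.

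Formulas:
- DE = 1 + (m − 1) × ICC
- Understatement of the SE = 1 − 1/√DE
- True size of a nominal 5% test = 2 × (1 − Φ(1.96/√DE))

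| m | ICC | DE | SE understated | True size (formula) | True size (simulation, 14 PHCs, baseline covariate) |
|---|---|---|---|---|---|
| 10 | 0.05 | 1.45 | 17% | 10.4% | 11.0% |
| 30 | 0.05 | 2.45 | 36% | 21.0% | 21.0% |
| 10 | 0.01 | 1.09 | 4% | 6.0% | 6.0% |
| 30 | 0.01 | 1.29 | 12% | 8.4% | 9.3% |

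**Does the baseline covariate rescue the model?** A second simulation (4,000 trials per setting, 7 PHCs per arm, no true effect) fitted a patient-level linear model on arm and baseline score without a cluster term. The patient-level baseline to follow-up correlation was assumed to be 0.5. The correlation of PHC effects between baseline and follow-up was varied.

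| m | ICC | PHC correlation 0 | 0.5 | 0.9 |
|---|---|---|---|---|
| 20 | 0.01 | 8.2% | 7.9% | 6.4% |
| 20 | 0.05 | 22.4% | 16.3% | 9.9% |
| 50 | 0.01 | 14.3% | 10.3% | 8.0% |
| 50 | 0.05 | 38.1% | 28.3% | 17.6% |

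The covariate helps more when PHC differences persist from baseline to follow-up, but in no setting did it bring the test back to 5%. A t-test (12 df) on baseline-adjusted PHC means from the same data rejected 4.4% to 5.5% of the time.

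**The case against.** A reader might infer that the protocol commits to linear models that ignore clustering. The document does not establish that, for four reasons.

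- The sentence on cluster effects refers to the models without restriction and sits among the patient-outcome analyses. It can be read as covering the linear models too. Its grammar also lets cluster adjustment stand apart from the optional age and gender covariates, so it is not shown to be merely optional.
- The text says linear regression. It does not say ordinary least squares, and it does not exclude a random effect or robust variance.
- The baseline clause speaks of *baseline* differences between clusters, and a baseline score does address those. The clause makes no claim about residual correlation.
- The ICC of 0.05 belongs to the screening outcome, so the inflation at that value is illustrative for WHODAS 2.0 and GAD-7.

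The article also refers to a statistical analysis plan (Ethical considerations), where the form of cluster adjustment and the degrees of freedom would normally sit. Their absence here is not a fault.

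All of this limits the point, but it does not remove it. The cluster-adjustment sentence comes before any mention of the linear models, and those models then receive their own, different device for cluster differences. The more natural reading leaves them without cluster adjustment, and the wider reading has to be supplied by the reader.

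**Conclusion.** The point holds as a conditional one. The wording for WHODAS 2.0 and GAD-7 gives no clear provision for correlation within PHCs, and on its natural reading gives none. If the baseline score is the only provision, inference will be too optimistic. Assuming 10 to 30 patients per PHC, a nominal 5% test rejects about 10% to 21% of the time at ICC 0.05, and about 6% to 9% at ICC 0.01. The direction is certain for any positive correlation that remains after adjustment. The size depends on enrolment and ICC values that the document does not state. If the cluster-adjustment sentence was meant to cover the linear models, the defect is one of wording only.

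These are secondary outcomes in a hybrid type III trial, and the primary outcome is not touched. The point is worth correcting but does not threaten the main conclusion.

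**What to change.** State that all three patient-outcome models, including the linear ones, account for PHC clustering. Either of these would serve:
- a PHC random effect with Kenward-Roger or Satterthwaite inference for the linear models and a matching small-sample provision for the logistic one; or
- a t-test on covariate-adjusted PHC means.

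Include the high/low footfall stratum used in the randomisation. For a cluster-level analysis this leaves 14 − 2 − 1 = 11 df. Keep the baseline score as a covariate for precision and baseline imbalance, and say that it is additional to cluster adjustment and not a substitute for it. Word cluster adjustment so that it cannot be read as one of the optional covariates.

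The change is a sentence or two and needs no new data. The Trial status section places the primary analyses after closeout. The cost is wider intervals for the secondary patient outcomes.

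### The only significance threshold in the protocol is printed as p<0.5, which allows a 50% type I error per test and does not fit the stated 80% power

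*Protocol article*

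**What the plan says.** The last sentence of the Statistical analysis section names the software and then gives the decision rule: p-values "<0.5 will be considered statistically significant". The article gives no other significance level, no confidence level and no sidedness.

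The Sample size estimation section gives the rest of the design but no alpha. It says "This sample size will allow us to detect a 15% difference in the proportion of PHQ-2 screenings between arms". Behind that statement lie a control-arm screening rate of 10%, power of 80%, a coefficient of variation of 0.5 and an ICC of 0.05. The target is a "25% screening rate in the intervention arm, or a 15% between-arm difference in screening rates", with "about 13,494 outpatients available for screening in each arm". There are seven facilities per arm.

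The design is described as a "cluster-randomized controlled superiority trial design". Tables 3 and 4 word several secondary hypotheses in terms of a significant difference: refusal of screening, treatment initiation, remission on the PHQ-9, WHODAS 2.0 and GAD-7.

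**The concern.** A threshold of 0.5 is ten times the conventional one. A superiority claim on the primary outcome would then need only a test statistic slightly larger than its median absolute value under no effect, so a null result would be called positive half the time. The same rule would cover each secondary outcome that is formally tested.

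The article also specifies the power of the primary comparison, so the threshold can be checked against the design. If the 80% power had been computed at 0.5, the printed value might have been deliberate. If it can only be obtained near 0.05, the two sections conflict and the printed threshold is the one in error.

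The Trial status section reports closeout in April 2024 with the primary analyses still to come. A wrong published threshold leaves readers unable to check the eventual claim against a rule fixed in advance.

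**Working it through.** **Inputs (Sample size estimation section unless noted)**
- Patients available per arm: 13,494. This agrees with the article's footfall: 14,994 × 0.9 = 13,494.6.
- Clusters: 7 per arm (Facility eligibility and recruitment section), so m = 13,494 / 7 = 1,927.7.
- ICC = 0.05; CV = 0.5, read as variation in cluster size.
- Screening rates: 10% versus 25%.
- Assumptions: two-sided test; 14 − 2 = 12 degrees of freedom for a cluster-level comparison.

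**Step 1. Reproduce the stated power**
- Design effect = 1 + ((CV² + 1) × m − 1) × ICC = 1 + (1.25 × 1,927.7 − 1) × 0.05 = 121.4.
- Effective sample per arm = 13,494 / 121.4 = 111.1.
- SE of the difference = √[(0.10 × 0.90 + 0.25 × 0.75) / 111.1] = √(0.2775 / 111.1) = 0.0500.
- Non-centrality = 0.15 / 0.0500 = 3.00.

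| Two-sided alpha | Power, t with 12 df | Power, normal (pooled null variance) | Power, normal (unpooled) |
|---|---|---|---|
| 0.05 | 78.7% | 84.2% | 85.1% |
| 0.5 | 98.9% | 99.0% | 99.0% |

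The stated 80% lies between the t and normal results at 0.05. It is far from any result at 0.5.

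**Step 2. Sensitivity to what the article leaves open**
- No variation in cluster size (CV = 0): 86.8% (t) or 91.2% (pooled normal) at 0.05; 99.6% by either method at 0.5.
- CV read as between-cluster variation in screening rates (Hayes–Bennett): 83.6% with 7 clusters per arm, or 77.6% with one cluster per arm deducted, at 0.05; 98.8% and 98.0% at 0.5.
- One-sided 0.05 with CV = 0.5: 88.1% (t). One-sided 0.5: 99.9% (t).

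Every variant at 0.5 gives 98% or more.

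**Step 3. Difference detectable with 80% power (pooled normal approximation, CV = 0.5)**
- Two-sided 0.05: 10% versus 24.05%, a difference of about 14 points, close to the stated 15.
- Two-sided 0.5: 10% versus 16.9%, a difference of about 7 points.

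**Step 4. Error rates if the printed rule is followed**
- Type I error per test is 0.50 by definition. A null simulation of 14 clusters (40,000 runs, cluster-level t test) rejected in 50.6% of runs at p<0.5 and 4.7% at p<0.05.
- The critical value on 12 df falls from 2.179 to 0.695.
- With 10% screened in both arms, the SE of the difference is √(2 × 0.09 / 111.1) = 0.0402. The smallest difference called significant is 0.695 × 0.0402 = 0.028, or 2.8 percentage points. At 0.05 it is 2.179 × 0.0402 = 0.088, or 8.8 points.
- For the primary outcome plus the five secondary outcomes listed above, if all six were null and independent, the chance of at least one false positive is 1 − 0.5⁶ = 98.4%. The same sum at 0.05 gives 1 − 0.95⁶ = 26.5%.

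**The case against.** The strongest reply is that this is a dropped zero. Nothing suggests that anyone chose 0.5, the power calculation points to 0.05, and p-values and estimates once reported can be judged at 0.05 whatever the article says. That is very probably how the error arose. It does not remove the point: the value is printed as the rule, nothing else in the article overrides it, and it applies to the primary outcome.

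Four further objections hold in part.
- **Scope.** The rule does not reach everything measured. Readiness and coaching-process measures are only described, appropriateness, feasibility and fidelity are assessed qualitatively, and costs are not compared between arms. The 50% applies to the inferential tests.
- **The 98.4% figure.** Independence is implausible, because remission, WHODAS 2.0 and GAD-7 come from the same patients, and screening and refusal from the same registers. It also includes ordinary multiplicity, as the 26.5% at 0.05 shows. It is illustrative only; the 50% per test suffices.
- **Fit to 0.05.** The match is approximate and depends on the meaning of the CV and on the test used. The calculation excludes 0.5 firmly but supports 0.05 only to within several points of power.
- **The SAP.** It is not shown and may already state the intended level. That would cover a missing detail, but not a value the article states wrongly.

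**Conclusion.** The concern holds. The article's sole significance threshold is wrong as printed and conflicts with its own sample size section. Followed literally, it gives a type I error of 50% instead of 5% for each inferential comparison, including the primary one, and would accept a chance screening difference of about 2.8 points. The stated 80% power corresponds to a two-sided level of about 0.05 (78.7% to 85.1% with the CV read as cluster-size variation) and cannot be obtained at 0.5 (98% or more in every variant).

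The 50% figure needs no assumption beyond a valid p-value. The 2.8-point figure assumes 10% screened in both arms, the stated ICC and CV, and 12 degrees of freedom. The identification of 0.05 as the intended level assumes a two-sided test. Whether the SAP repeats the error is unknown.

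**What to change.** In the Statistical analysis section, replace the threshold with a two-sided significance level of 0.05. Give the same level and sidedness in the Sample size estimation section, so that the power statement and the decision rule can be read together. Check the SAP and align it if it carries the same figure.

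Publish the correction before the primary analysis is run. If the analysis has already been done, date the correction and cite the SAP version that fixed the level, so that the threshold is seen not to depend on the results.

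The cost is a one-line correction to the article and a check of the SAP. No change to sample size, data collection or analysis model is needed.

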### Ethical considerations

Institutional Review Boards (IRB) at Harvard Medical School, United States and Sangath, India have approved all study procedures. Additional approval was obtained from the Government of India's Health Ministry Screening Committee, housed at the Indian Council of Medical Research. Written informed consent will be mandatory for enrolling patients in this trial. Participation in the study is completely voluntary and patients can decline participation or withdraw at any time without any consequence to their care at the PHCs. The confidentiality of participants will be protected using unique study ID numbers, and by separating study data from any identifiable data. An independent Data and Safety Monitoring Board (DSMB) will examine accumulating data to assure protection of participants’ safety and data integrity throughout the trial. The research team will submit regular progress reports, including serious adverse event (SAE) reporting, CONSORT flow charts, and baseline characteristics of enrolled participants across study arms to the DSMB. The DSMB will meet before the start of the trial, at the trial mid-point, and at the end of the study to review the statistical analysis plan. The team will maintain a Regulatory Binder containing all required regulatory documents that will be available at any time for study audit. Regulatory files will be checked at the research site for compliance prior to initiation of the trial, throughout the trial, and at trial closure. Study investigators will verify that study procedures are followed and that study staff are trained and able to conduct the protocol appropriately.

From the perspective of collecting mental health data in a rural setting, all participants’ baseline and endpoint assessment and consent records will be kept in password-protected computers/servers. All physical copies of documents will be kept in locked cabinets located inside the Sangath office. All data containing personal identifiers of participants will be delinked by removing all direct identifiers and assignment of a unique ID, combining all main indirect identifiers. We will train and conduct periodic refresher trainings of outcome assessors to manage situations of emotional distress that the participants may experience during the assessments and we will put in place, referral pathways to report distress such as to the medical officer in the primary health centre and the psychiatrist at the district hospital (note that the enhanced implementation support intervention is delivered to the facility teams and not the patients). This will also include management of reported instances of severe adverse events such as reported suicidal ideations/attempts, which the research team will come to know at the patient's three-month follow-up assessment. A study psychiatrist based at Sangath or a tertiary hospital in Bhopal will contact the participant within 24 h of receiving the SAE report, facilitated by the study team if required, to arrange a convenient time and place to complete a detailed assessment either by phone or face-to-face within 7 days, to assess relatedness to trial procedures, and offer any necessary intervention. Finally, we will make sure that outcome assessors receive refresher trainings on administrating informed consent in the rural setting, especially for situations such as reaching out to appropriate legally appointed representatives (family members) in cases of illiterate patients, to avoid sensitive situations where depression screen positivity is potentially disclosed to others in the participant's neighbouring community.

